### Sample size

Based on our previous work [19], we calculated, using the General Linear Multivariate Model Power and Sample Size software (GLIMMPSE), that a total sample size of 70 participants (n = 35 per treatment arm) yields sufficient power (80%) to detect the previously found effect of SCFAs on the cortisol response to an acute stress paradigm. Given that no information is available to calculate the effects of SCFAs on stress-induced cortisol response in patients with AN where greater variability might be present, we increased the sample size to 80 participants (n = 40 per arm). Based on a sensitivity power calculation (G*Power 3.1.9.2 software), 40 participants per arm would enable us to achieve 80% power to detect a small effect (Cohen's f = 0.16) in a within-between 2 (“visit”, baseline vs. post-intervention) × 2 (“treatment”, placebo vs. SCFA) mixed ANOVA model. Taking into consideration a 15% risk of dropout, we aim to recruit 92 individuals in total.

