### Other measures and questionnaires

During the hospital admission's final eligibility assessment, we will conduct the M.I.N.I-S International Neuropsychiatric Interview [48] to identify potential comorbid psychiatric disorders. Additionally, a self-developed questionnaire will gather information on demographic and clinical parameters. We will also maintain a comprehensive and detailed record of all medications, including antibiotics and any supplements, taken before and throughout the study.

The nursing staff at the hospital unit recurrently measures the participant's weight, while their height is measured during the initial visit. From these data points, we will systematically calculate BMI. In addition to monitoring their autonomic nervous system activity during the TSST, the wearable device will also track their physical activity during both study visits.

Participants will complete self-reported questionnaires on four occasions during the study: on the first, second, and third study visits and three weeks into the intervention between the first and second visits. Changes in eating disorder symptoms will be evaluated using the Eating Disorder Examination Questionnaire (EDE-Q) [49]. Additionally, restrained, emotional, and external eating behavior will be assessed by the Dutch Eating Behavior Questionnaire (DEBQ) [50]. 'Hedonic hunger' is measured through the Power of Food Scale (PFS) [51]. Furthermore, depressive symptoms, anxiety symptoms, affect, and stress will be assessed using the Depression, Anxiety, Stress Scales (DASS) [52], the Positive and Negative Affect Schedule (PANAS) [53], and the Perceived Stress Scale (PSS) [54]. Gastrointestinal complaints are scored using the Gastrointestinal Symptom Rating Scale (GSRS) [55] and the Rome IV questionnaire for functional gastrointestinal disorders [56].

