### Statistical analysis

#### Statistical methods for primary and secondary outcomes

The primary and secondary outcome variables will be analyzed using linear mixed models with “group” (placebo or SCFAs) as a between-subject factor and “visit” (pre- or postintervention) and, where appropriate, “timepoint” (measurement point within each visit) as within-subject factors. The group-by-visit and the group-by-visit-by-timepoint interaction effects constitute the principal effects of interest. If participants fail to exhibit an elevated cortisol stress response following stress induction, we will exclude their data from the analysis. To investigate the effect of the SCFAs intervention on treatment response, we will further control for BMI by including changes in BMI between visits 1, 2, and 3 in the linear mixed model as a continuous covariate. To investigate whether the changes in circulating SCFAs levels are mediated by the changes in the cortisol stress response to our stressor, we will pool all stress responders and enter the change in SCFA levels (post-intervention—pre-intervention) into the linear mixed model as a continuous covariate, including its interaction with visit, while omitting the group variable. The chosen significance level is alpha = 0.05. Follow-up planned contrasts will be conducted if there is a significant interaction effect and will be corrected for multiple testing comparisons using step-down Bonferroni (Holm) adjustment. Data of the intervention group will be further exploratively analyzed using linear mixed models with restrictive type AN and binge/purge type AN as “patient group,” investigating differences between the intervention of SCFAs between subtypes of patients with AN. In addition, we will enter the changes in questionnaires (baseline, post-intervention) into a linear mixed model as continuous covariates to investigate in an explorative way whether these changes (e.g., in AN severity, affect changes, subjective stress, etc.) are mediated by the changes in SCFAs levels and microbiota composition.

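### The exploratory questionnaire analysis asks whether symptom changes are mediated by SCFA and microbiota changes, but enters the symptom changes as covariates, so it cannot speak to mediation

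*Protocol article*

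**What the plan says.** The last sentence of the protocol article's section on statistical methods for primary and secondary outcomes gives both the model and its purpose. The model: "we will enter the changes in questionnaires (baseline, post-intervention) into a linear mixed model as continuous covariates". The purpose: "to investigate in an explorative way whether these changes", with AN severity, affect and subjective stress as examples, "are mediated by the changes in SCFAs levels and microbiota composition".

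The sentence does not name the dependent variable, and it does not say whether the questionnaires share one model or are taken one at a time. Earlier in the same paragraph, the analysis linking SCFAs to cortisol enters SCFA change as the covariate, with its interaction with visit, and leaves group out.

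The section on other measures and questionnaires lists eight instruments: EDE-Q, DEBQ, PFS, DASS, PANAS, PSS, GSRS and Rome IV. The sample size section sizes the trial "to detect the previously found effect of SCFAs on the cortisol response to an acute stress paradigm" and gives no figure for the questionnaires.

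**The concern.** Mediation of symptom change by SCFA or microbiota change implies a chain: treatment alters SCFAs or microbiota, and these alter symptoms. Symptom change is the end of that chain and belongs on the left of the model. The plan puts it on the right, and nothing in the sentence estimates the product of the two paths.

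The article presents SCFAs as mediators of microbiota-gut-brain interactions in its objective and aims, and this sentence is the stated analysis that carries the idea through to symptoms. Run as written, a significant coefficient could be reported as mediation although no indirect effect was estimated. A null result could be taken as evidence against mediation although mediation was not examined.

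**Working it through.** **1. The plan's own figure.** The article states "80% power to detect a small effect" (Cohen's f = 0.16) with 40 per arm in a 2 × 2 within-between model. With an assumed correlation of 0.5 between visits, λ = f² × N × m / (1 − ρ) = 0.16² × 80 × 2 / 0.5 = 8.19. On 1 and 78 degrees of freedom at α = 0.05, power is 80.7%, so the figure reproduces. With an assumed correlation of 0, 0.3 or 0.7 it would be 52%, 67% or 95%. This calculation concerns the treatment-by-visit design and says nothing about the questionnaire analysis.

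**2. Candidate dependent variables.**
- *Cortisol*, as in the primary model: symptom change would explain the stress response. Even if SCFA change is carried over as a further covariate, symptoms are still not the outcome.
- *SCFA level*: the proposed mediator is regressed on its supposed consequences.
- *Microbiota composition*: this is multivariate, and the sentence names no summary of it.

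None of the three has symptom change as the outcome, and none yields an indirect effect.

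**3. What is lost if each questionnaire is entered alone.** In a regression of one change score on another with no other terms, swapping sides leaves the test unchanged; a test data set of 80 gave p = 0.0014 both ways. The association is therefore still tested. At n = 80, 80% power is reached at |r| of about 0.30. This equivalence is for change on change. In a two-visit mixed model, the covariate's interaction with visit is needed to obtain it. The article states that term for the SCFA–cortisol analysis but not here.

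**4. What is lost if they are entered together.** Assumptions, none from the documents except n = 80: SCFA change is the dependent variable; each scale's change correlates r = 0.3 with it; k scales intercorrelate equally at c = 0.4 or 0.6. I take k = 7 (one score per instrument, without Rome IV) or k = 12 (the same with an assumed three DEBQ, three DASS and two PANAS scales).

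- Variance explained by k scales: R²(k) = k r² / (1 + (k − 1)c).
- One scale given the others: λ = n [R²(k) − R²(k − 1)] / [1 − R²(k)], on 1 and n − k − 1 df.
- Overall test: λ = n R²(k) / [1 − R²(k)], on k and n − k − 1 df.

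| k | c | R²(k) | R²(k − 1) | Power, one scale | Power, overall test |
|---|---|---|---|---|---|
| 7 | 0.4 | 0.185 | 0.180 | 11% | 86% |
| 7 | 0.6 | 0.137 | 0.135 | 7% | 69% |
| 12 | 0.4 | 0.200 | 0.198 | 7% | 80% |
| 12 | 0.6 | 0.142 | 0.141 | 6% | 57% |

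For one scale in its own model, λ = 80 × 0.09 / 0.91 = 7.91 and power is 79%; simulation gives 76–79%.

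**5. Why group must stay in the model.** Suppose there is no mediation, and treatment shifts SCFA change by 1.0 SD and symptoms by 0.5 SD independently (assumed). With 1:1 allocation the covariance induced by treatment alone is 0.25 × 1.0 × 0.5 = 0.125. The correlation is then 0.125 / √(1.25 × 1.0625) = 0.108. At n = 80 a model without group flags this in about 15–17% of simulated trials, against about 5–6% with group included.

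**The case against.** The strongest reply is that the article condenses a fuller plan, that the analysis is declared exploratory, and that full model terms may sit in an analysis plan not shown. On that view the unnamed dependent variable alone would be no finding. But the article does fix the role of the questionnaire changes, and that role contradicts the question in the same sentence. An exploratory label excuses the absence of a power calculation and of confirmatory error control; it does not make a model fit a question it does not address.

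Other planned analyses cover neighbouring ground. As secondary outcomes, the questionnaires are analysed by group and visit, and the microbiome section plans correlations with host metadata under false discovery rate control. These address treatment effects and associations, but not mediation by SCFAs.

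Three stronger readings are tempting, and the documents do not support them:
- *That all questionnaires enter one model, so power is about 6%.* A single model with plural covariates allows this reading, but separate models are not ruled out. The comparison also sets a coefficient adjusted for the other scales against a marginal association, which are different quantities.
- *That the model could not find any link between SCFAs and symptoms.* Entered singly, the association test survives; entered jointly, the overall test keeps 57–86% power under the same assumptions.
- *That the analysis is defective because it is not powered.* An exploratory analysis needs no power statement.

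It is also fair to say that 78% is not the power for an indirect effect. A simulation requiring both paths to be significant gave about 18%, 40% and 59% for treatment effects on SCFA of 0.3, 0.5 and 1.0 SD. It assumed two microbiota covariates correlated 0.3 with SCFA change and made no multiplicity correction. Nor would the corrected model establish temporal order, because both changes span the same six weeks.

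**Conclusion.** The point holds as a mismatch between question and model. Symptom change is on the predictor side and no indirect effect is estimated, so the mediation question goes unanswered whatever the result. This conclusion rests on the wording alone and needs no numerical assumption.

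The size of the further loss depends on an unstated choice. With single entry against SCFA change, it is confined to direction and mediation. With joint entry, the test of any one scale becomes nearly uninformative, under assumed correlations. A reader might infer that the trial's main conclusion is at risk, but the primary cortisol analysis does not depend on this sentence. The matter is moderate at most, and worth correcting because it is cheap to correct.

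**What to change.** Reword the sentence so that each questionnaire has its own model. The dependent variable is the post-intervention score (or the change), and the predictors are group, baseline score and SCFA change, or a microbiota summary named in advance. Keep group in the model.

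Then choose one of two courses: estimate the indirect effect (treatment to SCFA or microbiota, and from there to symptoms) with an interval, or drop the mediation wording and claim association only. Keep the exploratory label and correct across questionnaires. The article sets "The chosen significance level is alpha = 0.05", and eight independent unadjusted tests at that level would give a family-wise error of 1 − 0.95⁸ = 0.34. The Benjamini–Hochberg method already named for the microbiome data would serve.

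The cost is one rewritten sentence and slightly more analysis work. No new data are needed.

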#### Statistical methods for analyzing microbiome data

Pre-aliquoted fecal pellets are used for DNA extraction. Projected –omics analyses include metabolomic analysis, 16S/18S/ITS amplicon sequencing, transcriptomic, and metagenomic analysis. Statistical analyses on the microbiota will include estimation and comparison of microbiota diversity indices (observed richness, Shannon Index, Inverse Simpson Index, Pielou’s evenness index), samples' overall composition comparisons (using constrained ordination methods, such as principal coordinates and redundancy analysis), between-group analyses, and correlations with host metadata considering known confounders (such as weight loss and metabolic health) by using generalized linear models. Multiple testing corrections (Benjamini–Hochberg FDR) will be performed where applicable.

### Data management and monitoring

We will store data according to the ‘Research Data Management’ policy of KU Leuven. Research data will be collected and stored in an electronic case report form (eCRF) in the secure encrypted KU Leuven webserver. All data will be pseudonymized, with a key, only accessible to the primary researchers. Data gathered outside the eCRF will be collected under the pseudonym and later added to the eCRF. Investigators will promptly record any adverse events reported by the participant or observed by trial staff in the eCRF after detection. There are no plans for carrying out interim analyses. The UZ Leuven Clinical Trial Center assessed the clinical trial's risk and categorized it as having ‘comparable risk.’ This means that the potential risks associated with the study procedures and protocol design are deemed comparable to those of standard medical care. As a result, the trial's Sponsor decided that monitoring activities are not necessary. However, the Sponsor and the research ethics committee retain the right to audit and request source data from the trial at any time. The Sponsor or the principal investigator may terminate the trial prematurely at any time.

### Ethical aspects

The study is approved by the Medical Ethics Committee at the University Hospital Leuven in Belgium (reference S66404) and will be conducted in accordance with the Declaration of Helsinki. Prior to their admission into the research study, all participants must give their informed consent in a written format. Participants have the right to withdraw from the trial whenever they wish without incurring any disadvantages.

## Discussion

This protocol proposes a randomized control trial (RCT) using colon-delivery capsules (CDCs) to examine the effects of gut microbiota-affiliated metabolites, specifically SCFAs, on the stress response, eating behavior, and nutritional state in malnourished patients with AN. We focus on SCFAs for three primary reasons: First, preclinical data have evidenced the potential of SCFAs to modulate gut-brain interactions. Second, emerging research in healthy individuals has indicated that SCFAs can influence psychophysiological functions, including the stress response. Third, observed alterations in the gut microbiota composition of individuals with AN suggest a potential dysregulation in the production or utilization of SCFAs within this population. The employment of an RCT design paired with the use of CDCs allows us to examine the role of SCFAs in a mechanistic way. By administering SCFAs via CDCs, we ensure their direct delivery to the colon—their natural site of production—thereby enhancing the mechanistic insight to be gained from the study while maintaining its ecological validity.

Examining individuals with AN presents a distinct chance to explore the intricate interplay among the gut, brain, and behavior in psychiatric disorders, as eating disorders are most closely tied to nutrition and gut microbiota. Considering this, targeting the gut microbiota as part of AN treatment in the future could potentially be valuable in modulating the stress response, food choice, appetite, and neuropsychological functioning, among other outcomes.

## Data Availability

The datasets generated and/or analyzed during the current study are available from the corresponding author upon reasonable request.

## Abbreviations

ACTH: Adrenocorticotropin hormone
AN: Anorexia nervosa
BMI: Body mass index
CDCs: Colon-delivery capsules
DASS: Depression, anxiety, stress scales
DEBQ: Dutch eating behavior questionnaire
DSM-5: Diagnostic and statistical manual of mental disorders, 5th edition
eCRF: Electronic case report form
FCT: Food choice task
GLIMMPSE: General linear multivariate model power and sample size software
GSRS: Gastrointestinal symptom rating scale
HPA axis: Hypothalamus–pituitary–adrenal axis
IV: Intravenous
PANAS: Positive and negative affect schedule
PASA: Primary appraisal and secondary appraisal scale
PFS: Power of food scale
PSS: Perceived stress scale
RCT: Randomized controlled trial
sAA: Salivary alpha-amylase
SAM: Sympatho-adrenal medullary pathway
SCFAs: Short-chain fatty acids
TSST: Trier social stress test
UPC Z.Org: University Psychiatric Hospital Leuven
